| Surgical Morbidity d          |                        |                        |                          |                    |     |                     | X                    |                                                            | X                      |    |    |                             |
| Pathology e                   |                        |                        |                          |                    |     |                     | X                    |                                                            |                        |    |    |                             |
| Chemotherapy                             |                        |                        |                          |                    |     |                     |                      | X end of each cycle                                        |                        |    |    |                             |
| Toxicity assessment                      |                        |                        |                          |                    |     |                     |                      | X end of each cycle                                        | X                      |    |    |                             |
| Annual Follow-up                         |                        |                        |                          |                    |     | X                   |                      |                                                            | X                      | X  | X  | X                           |
| Adverse events f              |                        |                        |                          | X                  |     | X                   | X                    | X end of each cycle                                        |                        |    |    |                             |
| Concurrent medications                   |                        | X                      | X                        | X                  |     | X                   | X                    | X end of each cycle                                        |                        |    |    |                             |

The **X** also denotes that CRFs need completing - tick or initial the boxes as the CRFs are completed.

a Eligible subjects will be asked to provide written informed consent at registration and at randomization.

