| Annual follow-up                    |                              |                           |                             |                             |     |                                                                            |                                                                                                                                                                                                                                                                                                                                                                                                                                     |                                           |                            |                                                                     | X                      | X  | X  | X  |                                |

|                             |  |   |   |   |  |                     |  |   |   |                     |   |  |  |  |
|-----------------------------|--|---|---|---|--|---------------------|--|---|---|---------------------|---|--|--|--|
| Adverse events g |  |   |   | X |  | X end of each cycle |  |   |   | X end of each cycle |   |  |  |  |
| Concurrent medications      |  | X | X | X |  | X end of each cycle |  | X | X | X end of each cycle | X |  |  |  |

The **X** also denotes that CRFs need completing - tick or initial the boxes as the CRFs are completed.

a Eligible subjects will be asked to provide written informed consent at registration and at randomization.

b if patient has consented to additional blood sample collection for research.

c The post-CRT MRI should to be performed within 4-6 weeks (maximum of 10 weeks) from completion of CRT.

d Both early (4-6 weeks) and late surgical complications (up to 12 months) will be recorded.

e Resected specimen will be prepared and evaluated using a standardized method described in Appendix 5.

f Chemotherapy toxicity is assessed every 6 weeks during chemotherapy treatment. 12 weeks (6 cycles of FOLFOX or 4 cycles of CAPOX) are given pre-operatively and 12 weeks (6 cycles of FOLFOX or 4 cycles of CAPOX) are given post-operatively.

g All adverse events will be recorded from the date the Post-CRT MRI scan is performed until 30 days after the last dose of chemotherapy is administered during the Intervention Phase of the trial.

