## **2 REPORTING PROCEDURES FOR ALL ADVERSE EVENTS**

The investigator is responsible for ensuring that all adverse events (including SAEs) observed by the investigator or reported by patients from the date of the post-CRT MRI scan is performed until 30 days after the last dose of chemotherapy is administered are properly captured in the patients' medical records (source documents). Adverse events occurring in all arms of the trial should be reported with the same diligence so that bias is not introduced to the apparent incidence of adverse events observed in the intervention arm. In addition, the investigator is responsible for ensuring that, for those patients randomised, all adverse events captured on the patients' medical records (as specified above) are reported on the CRF.

**NOTE: The rationale for commencing AE recording from the date of the post-CRT MRI rather than the date of randomization is to avoid capturing AEs during and shortly after the last two weeks of CRT i.e. those that could be possibly related to CRT rather than the IMP(s) (systemic chemotherapy) received as part of the trial, which patients do not receive until after the post-CRT MRI scan is performed 4-6 weeks after the completion of CRT.**

As per assessment schedules residual toxicity will be assessed at the 12 month clinic visit.

In the TRIGGER trial, the seriousness, causality and expectedness of all adverse events will be assessed by the principal investigator (or delegate) at the participating site. Upon receipt at the trial management centre, all SAEs will be also reviewed by the Chief Investigator and CTIMP Lead at the Royal Marsden (or delegate).

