## **ADVERSE EVENTS AND SERIOUS ADVERSE EVENTS RELATED TO SURGERY**

Surgical adverse events and serious adverse events have been translated into complications. As surgery takes place during the Intervention Phase of the trial adverse events related to surgery should also be recorded on the **ADVERSE EVENTS Form**. Investigators should record on the **ADVERSE EVENT Form** whether the AE is related to systemic chemotherapy or surgery. A list of expected surgical complications is included in Section 2.3 below. Further information relating to early and late surgical complications will be captured on the **SURGICAL MORBIDITY Form**.

Please see section 2.1.4 regarding reporting of involved surgical resection margins (pCRM involvement).

For deferral of surgery the only adverse event of interest is **unsalvageable regrowth** (definition in section 11.3). This will be detected by the MDT during follow up. If it occurs this should be recorded on the **ADVERSE EVENT Form** and it is *definitely related* to deferral of surgery. A **SURVEILLANCE Form** should also be completed.

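### The poor-responder schedule (10.3) omits the adverse-event form at surgery and surgical follow-up, and its footnote f contradicts its own per-cycle toxicity row, so peri-operative capture may differ between arms

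*Protocol*

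**What the plan says.** Three assessment tables (sections 10.1 to 10.3) tell sites which forms to complete and when. Each states that an X "also denotes that CRFs need completing".

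- **Control, 10.1.** The adverse-event row is marked at the post-CRT visit, at surgery, at surgical follow-up and at the end of each adjuvant cycle.
- **Intervention, poor response, 10.3.** The adverse-event row is marked at the post-CRT visit and at the end of each pre-operative and each adjuvant cycle. The surgery and surgical follow-up cells are blank.
- **Intervention, good response, 10.2.** This pathway has no planned operation. If surgery happens, the table refers the site to the control schedule.

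The recording window is worded identically in 10.1 (footnote f) and 10.3 (footnote g): "All adverse events will be recorded from the date the Post-CRT MRI scan is performed until 30 days" after the last intervention-phase chemotherapy dose. Appendix 1, section 2, adds "Adverse events occurring in all arms of the trial should be reported with the same diligence so that bias is not introduced". Its paragraph on surgical events says that "adverse events related to surgery should also be recorded on the" Adverse Events Form, with no arm exempted.

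On toxicity, footnote f of 10.3 reads "Chemotherapy toxicity is assessed every 6 weeks during chemotherapy treatment". The toxicity row and timeline of the same table, section 8.3 and the opening list of section 10 all place the assessment at the end of every cycle.

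**The concern.** Site staff fill in forms from the schedule tables. The tables themselves invite them to tick or initial each box as the form is done. A blank cell is therefore a missing prompt, and here it is missing in one arm only, at the point where surgical events arise.

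Section 4.4.2 plans a between-arm comparison of grade 3-5 adverse events. Section 14.2.2 lists the acute-toxicity comparison under poor responders (mrTRG 3-5), the subgroup whose table lacks the marks. The results are meant to inform the phase III design. If peri-operative events are recorded more completely in controls than in intervention poor responders, part of any difference would reflect form completion rather than safety. Events not written down at the time are hard to recover at analysis.

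**Working it through.** **1. Is the blank real?** In 10.3 the concurrent-medication row, directly below the adverse-event row, has an X at both surgery and surgical follow-up. The two columns are therefore present in the table as read, and only the adverse-event cells are empty.

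**2. Count the adverse-event form points.** The Protocol's cycle numbers reproduce: 12 weeks / 2 = 6 FOLFOX cycles and 12 / 3 = 4 CAPOX cycles, so 12 and 8 over 24 weeks.

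| | CAPOX | FOLFOX |
|---|---|---|
| Control: post-CRT + surgery + surgical follow-up + cycles | 1+1+1+8 = 11 | 1+1+1+12 = 15 |
| Poor response: post-CRT + pre-operative + adjuvant cycles | 1+4+4 = 9 | 1+6+6 = 13 |
| Poor response with the two marks added | 11 | 15 |

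The whole difference is the two peri-operative points.

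**3. How long is the stretch without a prompt?** Section 8.3 puts surgery 6-12 weeks after pre-operative chemotherapy. Appendix 2, section 1.1, starts adjuvant treatment 4-12 weeks after surgery. The next form comes at the end of the first 2- or 3-week cycle. The gap is 6+4+2 = 12 weeks at the shortest and 12+12+3 = 27 weeks at the longest. Control patients have two prompts around their operation.

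**4. Does the common recording window close the gap?** It does for patients who start adjuvant chemotherapy, because surgery then lies inside the window. For a poor responder who never starts it, the last dose is pre-operative. Read literally, the window closes 30 days (4.3 weeks) later, before surgery at 6-12 weeks. Appendix 2, section 1.1, foresees that post-operative complications may put adjuvant treatment in doubt.

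**5. Toxicity frequency.** Footnote f alone gives 24 / 6 = 4 assessments. The table row gives 8 (CAPOX) or 12 (FOLFOX), the same as control. The amendment history records a change from six-weekly to per-cycle form completion at Version 3.0, so footnote f looks like text that was not updated.

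**6. Scale under assumed rates.** The Protocol gives no event rates. Let p be the chance of a grade 3-5 chemotherapy event and s that of a grade 3-5 peri-operative event, independent of each other, and suppose every peri-operative event is lost. The observed proportion among operated poor responders then falls by s x (1 - p). With p assumed at 20-40% and s at 5-20%, the range runs from 0.05 x 0.60 = 3 points to 0.20 x 0.80 = 16 points. This shows the scale of a worst case and is not an estimate.

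**7. A force the other way.** The window runs from the MRI (4-6 weeks after CRT) to 30 days after the last chemotherapy. Assume the first step after the MRI (surgery in control, chemotherapy in poor responders) falls 6-12 weeks after CRT.
- Control: 6+4+24+4.3-4 = 34.3 weeks to 12+12+24+4.3-6 = 46.3 weeks.
- Poor response: 6+12+6+4+12+4.3-4 = 40.3 weeks to 12+12+12+12+12+4.3-6 = 58.3 weeks.

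Poor responders are observed 6-12 weeks longer, which tends to raise their count.

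**The case against.** The strongest reply is that the Protocol as a whole does not ask for less capture in poor responders. Footnote g demands continuous recording in the control arm's own words. Appendix 1 requires equal diligence and puts surgical events on the Adverse Events Form in every arm, and non-exempt serious events must be reported within 24 hours whatever the table shows. The tables are also loosely drafted elsewhere: 10.1 has an annual follow-up mark in its surgery column. This stands. The defect is a table that contradicts the governing text, not a decision to collect less.

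The link to the endpoint is also open to question. Section 4.4.2 speaks of adverse events, but under an acute-toxicity bullet. The Fisher test in section 14.2.2 is on toxicity. Surgical morbidity has its own form, marked at surgical follow-up and 12 months in both tables, and its own Clavien-Dindo comparison. If the grade 3-5 analysis uses only the per-cycle toxicity forms, the missing marks hardly touch it. This stands as a limit on the consequence. It does not remove the contradiction, because the morbidity form does not use the CTCAE grades of the toxicity endpoint, and the Adverse Events Form is where attribution to chemotherapy or surgery is recorded.

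A reader might infer from footnote f that poor responders are graded for toxicity only half (CAPOX) or a third (FOLFOX) as often as controls. The documents do not support that. The footnote is attached to the chemotherapy row, and the toxicity row, the timeline, section 8.3 and section 10 all say every cycle.

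**Conclusion.** The point holds as an inconsistency that sites could act on. The 10.3 adverse-event row lacks two peri-operative form prompts that 10.1 has and that Appendix 1 implies, and footnote f of 10.3 conflicts with the rest of the Protocol. If sites follow the printed table, peri-operative adverse events risk being recorded less completely in intervention poor responders than in controls, which could distort an exploratory comparison.

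A reader might go further and conclude that the comparison is biased in favour of the intervention. That is not shown. It requires sites to follow the table over Appendix 1 and the analysis to include surgical events. The longer recording window in poor responders pushes the other way. The Protocol states neither the number of operated poor responders nor any event rate, so a count of missed patients would rest wholly on assumption and would have to allow for patients already counted through a chemotherapy event. Neither size nor net direction can be derived. The trial's primary endpoint, the recruitment rate, is unaffected.

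**What to change.** In the adverse-event row of 10.3, add the form mark at surgery and at surgical follow-up, so that it matches 10.1 and Appendix 1. Reconcile footnote f of 10.3 with the per-cycle assessment stated in the toxicity row of that table, section 8.3 and section 10, so that one frequency stands throughout and capture is the same in both arms.

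The cost is two table cells and one footnote. Both visits already exist in the schedule and already carry other forms, so no patient attends more often.

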## 10.4 BIOMARKER DEVELOPMENT

All patients will be asked to consent to the collection of additional blood samples at trial registration and randomisation for a translational sub-study (Appendix 7), which will be collected at the following time points:

- Registration
- 4-6 weeks post CRT
- For patients who undergo surgery:
  - 4-8 weeks post surgery
  - 3 months post surgery (for most patients this will be during adjuvant chemotherapy)
  - Annual follow-up visits at 12, 24 and 36 months.
- For patients who defer surgery
  - At follow-up visits (as per surveillance schedule) from end of CRT at 6, 9, 12, 18, 24, 30 and 36 months, and at 4 and 5 years.
- For all patients who relapse during trial:
  - Within 2 weeks of tumour relapse

Participants are also asked to consent to donate their diagnostic paraffin embedded tumour tissue (FFPE blocks) and H&E slides at registration and at the time of surgery to be used in the translational sub-study (Appendix 7) to evaluate the role of prognostic and predictive biomarkers. Details relating to the histopathology evaluation of the resected specimen can be found in Appendix 5.

### 10.4.1 BLOOD SAMPLES FOR BIOMARKER ANALYSIS

#### Site sample collection

The specimens should only be collected if the patient consents to the collection of a sample at registration and for follow-up samples at randomisation.

Label 2 x 10 ml cell free DNATmSteck tubes (Streck tubes) with the trial-specific label provided and add site number, patient ID number and initials, visit date and visit time-point. Blood samples should be collected at the time points outlined in section 10.4 above. Ideally this should occur at the same time as other blood tests in order to avoid the need for an additional venepuncture. Samples should be sent to the Royal Marsden within 48 hours of collection.

Please see the **Laboratory Manual** for full details on the collection, processing, storage and shipment of the blood samples. The manual also includes details of blood sample collection for patients who have co-enrolled into TRACC Trial.

## **Sample processing at RM**

At the RM, once the samples have been received they will be catalogued, processed and stored.

Further information on the collection, processing and storage of the blood samples at the lead centre can be found in the Laboratory Manual.

### **10.4.2 H&E STAINED GLASS SLIDES**

All of the H&E stained glass slides from both the original diagnostic biopsy and the surgical resection specimens should be sent to the Royal Marsden for scanning. Copies of the slides can be sent if the local site does not want to release the originals. Alternatively high resolution digital slides can be sent if slide scanning facilities are available locally.

### **10.4.3 PARAFFIN-EMBEDDED DIAGNOSTIC TUMOUR TISSUE**

Appropriately labelled tissue blocks of the original diagnostic biopsy should be sent to the Royal Marsden **within 28 days** of patient registration for central archiving, or at the time of randomisation if not sent previously. Blocks should also be sent at the time of surgery as detailed in Appendix 5.

Please see the **Laboratory Manual** for guidance on collection, processing, shipment and storage of the tissue samples.

This tissue will be used to assay for the presence of biomarkers which will be correlated to outcome and response to treatment to evaluate their potential prognostic and predictive role. Other biomarkers which will be examined are to be determined at a later date and may include components of signalling pathways which have a role in cancer development or progression.

### **10.4.4 SAMPLE PROCESSING AT ROYAL MARSDEN**

All blood and tissue samples will be stored at the Royal Marsden until analysis, which will take place at the end of the feasibility trial. Measurements of ctDNA will be carried out at the Institute of Cancer Research/Royal Marsden BRC. The H&E Slides will be sent to the Dept of Pathology and Tumour Biology at St James' Hospital in Leeds and will be digitised and archived. The FFPE blocks will be sent to the ICR/Royal Marsden BRC for DNA and RNA extraction and then sent to the University of Southampton for the preparation and analysis of tissue microarrays (TMAs). TMAs will be sent to the ICR/Royal Marsden BRC, St James' Hospital Leeds and the Institute of Molecular Sciences at Radboud University, Nijmegen for further analysis.

Following analysis, surplus blood and tumour tissue will be returned to the Royal Marsden for storage for future research, subject to funding and approval by members of the TMG.

### **10.4.5 SAMPLE LABELLING, STORAGE AND DESTRUCTION**

In order to protect patient identity, blood, paraffin embedded tumour blocks and H&E slides should not be labelled with any information which may lead to the direct identification of the patient concerned,

including patient name, date of birth, or National Health Service (NHS) or hospital number. Instead samples should be labelled with the study name, site number, the patient's study number (assigned at registration), and patient initials. The date of collection should also be recorded on blood samples. Centres should also keep a record of blood and tissue samples collected on the Blood & Tissue Sample Log (template included in the Laboratory Manual) which includes the same information. In addition, the date of transfer of samples to the lead centre should be recorded.

Prior to transfer to the lead centre, centres should ensure that blood and tumour samples are appropriately stored as detailed in the Laboratory Manual. Blood and tissue samples received by the lead site will be stored indefinitely. However, the patient retains the right to have the sample material returned to their hospital pathology department or destroyed at any time by contacting the principal investigator at the site at which they were registered for the study. The site principal investigator will then be responsible for contacting the sponsor via the chief investigator to arrange for the return or destruction of the samples.

The sponsor will be the exclusive owner of any data, discoveries, or derivative materials from the sample materials and is responsible, via the chief investigator, for the destruction of the sample(s) at the request of the research patient through the site principal investigator or at the end of the storage period. The site principal investigator will provide the chief investigator with the required patient study numbers so that any unused blood and tissue samples can be located and destroyed. If a commercial product is developed from this research project, the sponsor will own the commercial product. The patient will have no commercial rights to such product and will have no commercial rights to the data, information, discoveries, or derivative materials gained or produced from the sample.

## **11. CLINICAL FOLLOW-UP**

Once randomised, patients remain evaluable for the intent-to-treat analysis regardless of their subsequent course and treatment. Follow-up data on all patients, including details of other treatments given, is therefore important.

All patients that undergo surgery will be followed up for 5 years. Patients that defer surgery will be followed up for 10 years. In addition, where available, national mortality records and hospitals episodes statistics will be used to ensure long-term follow-up. If a patient fails to attend a clinic or cannot be followed up, the site should contact the patient's GP to assess their condition.

### **Summary of Clinical Investigations for all patients**

Clinical investigations performed prior to CRT, during CRT, before and after surgery and during chemotherapy should be performed as per standard clinical practice and as clinically indicated, including

but not limited to clinical examinations, performance status, vital signs , ECG, routine blood tests, pregnancy tests for women of childbearing potential, measurements of CEA (see section below), imaging and colonoscopy.

A baseline MRI and post-CRT MRI are mandatory for all subjects as included in the Assessments schedules in Section 10. Patients in the 'poor response' subgroup of the intervention arm should also receive a second post treatment MRI scan following pre-operative systemic chemotherapy and mrTRG reported for review at the MDT reassessment meeting (Section 10.3).

Patients managed with deferral of surgery require additional monitoring as detailed in section 11.2.1 below.

